#### Study arms

##### Opening the Conversation: experimental intervention group

The intervention group, OC, receives 5 weekly sessions with a trained interventionist. Session content is outlined in Table 1. Couples learn coping and communication strategies that increase their support for one another, particularly related to reproductive and sexual distress. The comparison arm, SS, provided a foundation for the development of OC, but OC was adapted to specifically address coping and communication about RSH concerns after cancer. Modifications were based on an iterative process of interviews with couples and stakeholder feedback. Briefly, these included new educational material about RSH-related concerns after cancer for both partners, integration of opportunity to discuss RSH topics across sessions, and the addition of a fifth session to give couples the opportunity to use new skills learned to discuss an RSH topic of their choice. Details about the systematic adaptation process and resulting changes are available elsewhere [56].

**Table 1 Tab1:** Opening the Conversation (OC) and Side by Side (SS) session summaries

Session	Opening the Conversation	Side by Side
1	• Introduction and overview • Cancer’s impact on relationships and RSH • Introduce educational materials on RSH concerns after cancer • Introduce supportive communication, supportive behavior, mindfulness	• Introduction and overview • Cancer’s impact on relationships • Introduce supportive communication, supportive behavior, mindfulness
2	• Stressors and stress response, with focus on RSH • Coping strategies and self-talk, with examples related to RSH • Practice supportive communication, focusing on an RSH stressor	• Stressors and stress response, with focus on cancer experience • Coping strategies and self-talk • Practice supportive communication, focusing on a cancer-related stressor
3	• Practice supportive communication, focusing on an RSH stressor • Communication with family/friends, with examples related to RSH • Patient advocacy and healthcare provider communication about RSH concerns	• Practice supportive communication • Communication with family/friends
4	• Sexual health concerns, emotional and physical intimacy • Communication exercise to build shared understanding about intimacy • Identifying and scheduling activities to support intimacy • Setting goals to support intimacy	• Emotional intimacy • Making time for activities to support relationship • Explore positive aspects of your cancer experience • Setting goals to support relationship
5	• Reproductive health and family building concerns • Practice supportive communication with RSH topic • Skill review • Setting goals to support relationship	None

##### Side by Side: active comparison group

The comparison group, SS, receives 4 weekly sessions with a trained interventionist. Session content is outlined in Table 1. Couples learn coping and communication strategies that increase their support for one another as they navigate cancer-related stressors in general. SS includes a discussion and exercise focused on emotional, but not physical, aspects of intimacy. SS was selected as a comparator because of its grounding in theory and evidence-based practice along with its demonstrated effectiveness for improving relationship and psychosocial outcomes among BGC survivors [34, 36, 49]. Original content was updated for virtual delivery to our intended audience, including use of inclusive language for LGBTQ+ couples.

### Measures

The outcome measures used are reliable and valid with cancer survivors. We selected short form versions, where available, to reduce participant burden. All outcome measures are assessed at 3 time points: baseline (immediately prior to intervention), 2 weeks after the last session, and 3 months after the last session. All outcome measures and assessment instruments are listed in Table 2.

**Table 2 Tab2:** Schedule of enrollment, interventions, and assessments

	Enrollment eligibility T0	Allocation baseline T1	Post-allocation			
			Sessions 1–4	Sessions 1–5	T2 2 weeks	T3 3 months
ENROLLMENT						
Eligibility screen	X					
Informed consent	X					
Allocation		X				
INTERVENTIONS						
OC intervention				X		
SS intervention			X			
ASSESSMENTS						
Primary outcomes						
Reproductive distress Fertility Problem Inventory (FPI)-Relationship Concern Domain		X			X	X
Sexual distress Sexual and Relationship Distress Scale (SaRDS)		X			X	X
Secondary outcomes						
Relationship functioning Dyadic Adjustment Scale (DAS-7)		X			X	X
Relationship intimacy Miller Social Intimacy Scale (MSIS)		X			X	X
Communication about reproductive concerns Couples’ Illness Communication Scale (CSIS)		X			X	X
Communication about sexual concerns Couples’ Illness Communication Scale (CSIS)		X			X	X
Sexual function (female) Female Sexual Function Index (FSFI)		X			X	X
Sexual function (male) International Index of Erectile Function (IIEF)		X			X	X
Sexual satisfaction General Measure of Sexual Satisfaction (GMSEX)		X			X	X
Depressive symptoms Patient Health Questionnaire Depression Scale (PHQ-8)		X			X	X
Health-related quality of life PROMIS Global 10 v1.2		X			X	X
Self-efficacy^a^ Self-Efficacy to Communicate about Sex and Intimacy (SECSI)		X			X	X
Mediating variables						
Dyadic coping	Dyadic Coping Inventory (DCI)	X			X	X
Communication quality	Communication Patterns Questionnaire- Short Form (CPQ-SF)	X			X	X

^a^Cancer survivor-only measure

Intervention acceptability and appropriateness and interventionist assessments are measured 2 weeks after the last session. Two process measures (perceived usefulness and session-specific evaluations) are measured during the intervention.

#### Primary outcome measures

##### Reproductive distress

Reproductive distress is measured using the Fertility Problem Inventory (FPI)-Relationship Concern Domain. This measure consists of 10 items assessing concerns about infertility’s impact on the relationship. Higher scores indicate a higher level of distress [59–61].

##### Sexual distress

Sexual and relationship distress is measured with the Sexual and Relationship Distress Scale (SaRDS), a 30-item, multidimensional scale that measures relationship distress within the context of sexual difficulties [62]. Item responses are summed to create a total summary score, with higher scores indicating more sexual distress.

#### Secondary outcome measures

##### Communication about reproductive concerns

Communication about reproductive concerns is assessed via the Couples’ Illness Communication Scale, a four-item scale adapted to measure couple communication about reproductive/fertility concerns [63]. Item responses are summed to create a total score, with higher scores indicating better reproductive-related couple communication.

##### Communication about sexual concerns

Communication about sexual concerns is also assessed via the Couples’ Illness Communication Scale [63], adapted to measure couple communication about sexual concerns. Higher scores indicate better sex-related couple communication.

##### Depressive symptoms

Depression is measured using the Patient Health Questionnaire Depression Scale (PHQ-8), an eight-item scale assessing depression severity [64, 65]. Higher scores reflect higher depressive symptoms.

##### Female sexual function

Female sexual function is measured via the Female Sexual Function Index (FSFI), a 19-item, multidimensional scale assessing the following domains of female sexual function including desire, arousal, lubrication, orgasm, pain, and satisfaction [66, 67]. Subscale scores are summed to create a total score, with higher scores indicating better functioning.

##### Male sexual function

Male sexual function is measured via the International Index of Erectile Function (IIEF), a 15-item, multidimensional scale assessing various domains of male sexual function [68, 69]. Item responses within each domain are summed to create subscale scores, and subscale scores are summed to create a total score, with higher scores indicating better functioning.

##### Relationship quality

Relationship functioning is measured with the Dyadic Adjustment Scale (DAS-7), a seven-item scale measuring relationship functioning [70]. Responses are summed to create a total score, with higher scores reflecting better relationship functioning [70–72].

##### Relationship intimacy

Intimacy is measured using the Miller Social Intimacy Scale, a 17-item scale that measures the level of intimacy currently experienced in an interpersonal relationship [73]. Responses are summed, with higher scores reflecting higher levels of intimacy.

##### Sexual satisfaction

Sexual satisfaction is measured with the General Measure of Sexual Satisfaction (GMSEX), a five-item scale assessing the sexual relationship, with higher scores indicating greater sexual satisfaction [74, 75].

##### Self-efficacy to communicate about sex and intimacy

Self-efficacy is measured for cancer survivors only using the Self-Efficacy to Communicate about Sex and Intimacy (SECSI) scale. This 10-item measure assesses cancer survivors’ self-efficacy for sexual health communication over the last month, with higher scores indicating higher self-efficacy [65].

##### Quality of life

Quality of life is assessed via the PROMIS (Patient-Reported Outcome Measurement Information Systems) Global 10-item scale, which measures aspects of physical and mental health. Scores are standardized to the general population [76, 77].

#### Intervention mediators

##### Dyadic coping

Dyadic coping is measured with the Dyadic Coping Inventory, a 37-item scale measuring perceived communication and dyadic coping among couples. This scale consists of several subscales measuring supportive, delegated, negative, and joint coping. Responses to each item are summed to create a total score, with higher scores indicating higher relationship quality [78, 79].

##### Communication quality

Communication quality is measured using the Communication Patterns Questionnaire-Short Form (CPQ-SF), an 11-item self-assessment measuring perceptions of relationship interactions. The CPQ-SF assesses different patterns of communication (non-constructive communication and constructive communication), with higher scores indicating more use of that communication pattern during conflict [80].

#### Demographics, cancer, and reproductive history

Socio-demographic characteristics including age at baseline, race, ethnicity, sexual orientation, gender identity, education level, number of children, and employment status are collected via self-report. Relationship, cancer, and reproductive characteristics are also assessed by self-report, including relationship status and duration, desire for children, cancer type, stage, and treatments, time since diagnosis, and reproductive history.

#### Acceptability, appropriateness, and feasibility

Intervention acceptability and appropriateness are assessed via AIM/FIM subscales [81] and a counselor assessment form. Perceived usefulness is assessed after the first session with items asking how logical the program seemed, how helpful they think the program will be, and how competent they believe the counselor is. Each week, participants are asked to assess the extent to which they interacted with and understood the program material.

### Statistical plan

We will compare recruitment, retention, satisfaction, and completion of assessments for the intervention and comparison group. Our approach to recruitment and retention minimizes missing data by monitoring and actively following up with reminders for survey completion, and by incentivizing participation. Initial analyses will examine characteristics of non-completers. As recommended by Lang & Little [82], multiple imputation (using 50 imputed samples) will be used to impute missing values for analyses using multilevel modeling (MLM) and full information maximum likelihood (FIML) will be used for mediation analyses conducted within a structural equation modeling framework.

Basic descriptive data analyses will be conducted to examine means, standard deviations, and correlations among the study measures. Normality of outcomes will be assessed, and data transformations will be applied as needed.

Multilevel modeling (MLM; SPSS Version 27) with REML will be used to test Aim 1a for both the primary (reproductive and sexual distress) and secondary outcomes (relationship outcomes and psychosocial health outcomes). These models will examine mean differences in outcomes between OC and SS over time (baseline, 2 weeks, 3 months) and across role (i.e., survivor versus partner) for outcomes measured from both partners. In our primary analyses, time, treatment, and role will be treated as categorical, and models will include all main effects and interactions among these variables. Evidence of treatment efficacy will be assessed by the interaction between time and treatment as we expect no treatment differences at baseline, but we expect to see such differences after the intervention. These models will include random intercepts for survivors and partners, as well as the correlation between the intercepts (i.e., if a survivor is high in average distress across time, is the partner high as well?). They will also include a time-specific correlation between the partners’ residuals (i.e., if a survivor is especially distressed at a particular time point, is the partner especially distressed at that time as well?). In addition to being able to model the interdependence between survivors and partners, the MLM approach has the advantage that it does not delete participants with missing data at some time points and so this analysis utilizes all available data. Outcomes measured only for survivors or only for partners will also be analyzed using MLM, but in this case role will not be included as a predictor and the random effects will include only a random intercept and residual variance.

Covariates to be assessed include age, time since diagnosis, cancer stage, metastatic status, number of children, relationship duration, income, race, ethnicity, and sexual orientation. To determine which covariates should be included in the analyses, preliminary analyses will be conducted in which each outcome is predicted by the full set of qualifying covariates. Only those covariates that predict at least one outcome significantly will be included in the analyses. Once the set of covariates are determined in this way, the same set of covariates will be included in all analyses.

Exploratory Aim 1b posits a mediational model in which the effects of the intervention on both partners’ primary outcomes are mediated by both partners’ dyadic coping and communication. To examine mediation, the statistical package MPLUS will be used to estimate and test the indirect effects of the treatment on 3-month outcomes via the patient’s and partner’s dyadic coping and communication measured 2 weeks after the intervention. The same set of covariates used in tests of Aim 1a will be included.

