### Procedures

#### Recruitment and informed consent

Study recruitment is multi-pronged in that it includes a range of sources of participant identification, including study advertisements online via social media platforms, outreach through community partners, and letters mailed to potentially eligible cancer survivors in the Oregon State Cancer Registry (OSCaR). This strategy was selected both to facilitate achieving recruitment targets and to reach a diverse sample of dyads nationwide in light of the differences in survivors found through these sources.

Consent is obtained electronically after both partners complete screening procedures and potential participants can discuss their questions with a member of the research staff. Once both members of the dyad have completed consent, the dyad is considered to be consented. Enrollment is determined at randomization, after both partners complete the baseline assessment.

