#### Randomization

The study uses 1:1 blocked randomization (groups of 4), stratified by cancer type (breast versus gynecologic) and sexual orientation reported by the cancer survivor (heterosexual versus other). The study statistician generates the randomization sequence, and assignment to condition occurs via REDCap after the dyad has completed both the baseline assessment and videoconference orientation call with study staff. Couples are notified of their intervention assignment after scheduling their first session with the study interventionist. At that time, they receive both a mailed version and link to an electronic version of the participant materials. As with most behavioral interventions, the study interventionist, intervention supervisor, and participants are not masked to condition. However, although participants know whether they are receiving OC or SS, they are not told which of these is the experimental condition. The condition is masked to the PI, biostatistician, and research assistants who will evaluate quantitative outcome data. Quantitative outcome data is also collected via REDCap to minimize contact with participants while collecting study data. Should a review of adverse events reveal significant between-group differences that could warrant unmasking of the study conditions by the study biostatistician.

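### The primary model estimates a free arm difference at baseline although randomisation follows baseline; the test stays valid, but it gives up precision that could be recovered at no cost

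*Protocol article*

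**What the plan says.** The Statistical plan section of the protocol article specifies a multilevel model with baseline, 2 weeks and 3 months as categorical levels of time. For time, treatment and role, the "models will include all main effects and interactions among these variables". The efficacy criterion follows: "Evidence of treatment efficacy will be assessed by the interaction between time and treatment as we expect no treatment differences at baseline". On the covariance the section says: "These models will include random intercepts for survivors and partners, as well as the correlation between the intercepts"; a same-time residual correlation between partners is added.

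Two other sections fix the order of events. Recruitment and informed consent states: "Enrollment is determined at randomization, after both partners complete the baseline assessment". Randomization states: "assignment to condition occurs via REDCap after the dyad has completed both the baseline assessment and videoconference orientation call".

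The candidate covariates are listed as follows: "Covariates to be assessed include age, time since diagnosis, cancer stage, metastatic status, number of children, relationship duration, income, race, ethnicity, and sexual orientation". The T1 score of the outcome is not among them. Table 3 gives 3 months as the time frame of both primary outcomes.

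**The concern.** A full factorial that includes a treatment main effect estimates a separate T1 mean for each arm within each role. Because T1 is measured before allocation, those two means are equal in expectation by design. The model spends a parameter per role on a difference known to be zero on average, and then subtracts that estimate, with its sampling error, from every follow-up contrast. The listed covariates do not repair this with complete data: a covariate that is constant over time and entered as a main effect cancels out of a change contrast.

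Precision is at stake. The trial has 100 couples, and the Discussion expects benefit in both arms, so the difference between arms may be modest.

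**Working it through.** **Inputs.** 100 couples, 1:1 allocation, partner correlation .4 and 20% attrition at the final assessment (Randomization; Sample size estimate/power calculations). Random intercepts plus residual give equal correlation ρ between any two visits of the same person. Assumptions of this check: ρ itself, two-sided alpha .05, unit variance at each visit, and partner correlation .4 for both intercepts and residuals.

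**The plan's own figures.** Effective sample size = individuals/(1+r): 200/1.4 = 142.9 and 160/1.4 = 114.3, matching the stated 142 and 114. For power, use the repeated-measures within-between interaction with f = d/2, λ = f²·N·3/(1−ρ), df = 2 and 2(N−2). At ρ = .4:
- N = 142, d = .27: λ = .135²·142·3/.6 = 12.94, power .903 (stated: 90%).
- N = 114, d = .30: λ = .15²·114·3/.6 = 12.83, power .900 (stated: 90%).
- N = 100, d = .32: λ = .16²·100·3/.6 = 12.80, power .899 (stated: 90%).

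At ρ = .3 the first two powers are .852 and .847; at ρ = .5 they are .949 and .947. The stated figures therefore imply ρ of about .4, but the article does not say so; its only stated correlation is the one between partners. The remaining figure, 80% power at d = .36 with 80 couples, computes to .901 at ρ = .4. That mismatch does not bear on this point.

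**Variance of the T3 effect, complete data.** Per person:
- free baseline: Var(Y3 − Y1) = 2(1−ρ)
- baseline constrained or adjusted for: Var(Y3 given Y1) = 1−ρ²
- ratio = (1−ρ²)/[2(1−ρ)] = (1+ρ)/2, so the loss is (1−ρ)/2.

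The partner correlation scales both models alike. Averaging two partners multiplies each variance by (1+.4)/2 = .70. With 50 couples per arm the arm difference multiplies it by 2/50 = .04. At ρ = .4:
- free: .04·.70·1.20 = .0336, SE .183
- constrained: .04·.70·.84 = .0235, SE .153.

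**With 20% missing at T3.** Generalised least squares on the six outcomes per couple (two roles, three visits):

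| ρ (assumed) | Loss, complete data | Loss, 20% missing at T3 |
|---|---|---|
| .3 | 35% | 30% |
| .4 | 30% | 26% |
| .5 | 25% | 21% |
| .6 | 20% | 17% |
| .7 | 15% | 13% |
| .8 | 10% | 8.5% |

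These are variance losses. On the standard-error scale with complete data they are about 16%, 13% and 11% at ρ = .4, .5 and .6, and 5% at .8. Other splits of the partner correlation change them little: intercept .6 with residual .2 gives 26.5% at ρ = .4 with complete data, and .2 with .4 gives 31.8%.

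**Detectable difference, 1-df T3 contrast, both-partner outcomes.** At ρ = .4 with 20% missing, the single-role SEs are .236 (free) and .203 (constrained). Multiplying by √.70 = .837 gives .197 and .170. Multiplying by 1.960 + 1.282 = 3.242 gives about .64 and .55 SD at 90% power.

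**The planned 2-df interaction test.** With complete data:
- Effect at T3 only: loss = 1 − (2/3)(1+2ρ)/(1+ρ), which is 14% at ρ = .4 and 4% at ρ = .8.
- Equal effect at T2 and T3: loss = 1 − (1+2ρ)/3, which is 40% at ρ = .4 and 13% at ρ = .8.

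With 20% missing at T3 these become 12% and 3% (T3 only), and 38% and 13% (equal effect).

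**The case against.** The strongest reply is that nothing here is wrong. After randomisation the interaction test is unbiased and keeps its type I error. The power section computes power for the treatment-by-time interaction, and its primary-outcome figures reproduce. Expecting no baseline difference is a coherent reason for testing the interaction. All of this stands, and it makes the point one of efficiency only.

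A reader might be tempted to go further in four ways that the documents do not support:
- **That a fixed share of precision, such as 20–30%, is discarded.** That range needs ρ between .4 and .6, complete data and a single visit. The documents give no ρ and plan for 20% attrition, and the efficacy criterion is an interaction over three visits.
- **That power is overstated.** The stated d values are on the scale of the interaction test (f = d/2). They must not be set against the .64 or .55 SD above, which refer to a difference at one visit.
- **That leaving the T1 score off the covariate list is a second fault.** Baseline is already an outcome in this model, so it should not also be a covariate in the same model.
- **That the model always analyses raw change scores.** This is exact only with complete data.

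The structure is not in dispute: the article itself commits to the full factorial and places allocation after T1, so this is not a detail left to an unseen analysis plan.

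**Conclusion.** The point holds as an efficiency improvement, worth making but not a condition for a valid trial. The plan leaves free a baseline difference that its own design sets to zero in expectation. For the 3-month effect the variance loss is (1−ρ)/2 with complete data: 35% to 10% over ρ = .3 to .8, and about 30% to 8.5% with the planned attrition. At ρ = .4, the value implied by the power figures if alpha is two-sided .05, the loss with attrition is 26%. For the 2-df test it is smaller if the effect appears only at T3 and larger if the effect is equal at both follow-ups. The sizes rest on the assumed ρ and on the random-intercept covariance that the plan specifies. The direction does not depend on the value of ρ, since the loss is positive for every ρ below 1.

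**What to change.** For all primary and secondary outcomes, constrain the OC and SS means to be equal at T1 within role. Keep the treatment effects at T2 and T3 (by role where both partners are measured), and test efficacy on those effects.

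In practice, code treatment as two numeric indicators, OC-at-T2 and OC-at-T3, both zero at T1, with role interactions, alongside time, role and time-by-role. Deleting the treatment main effect while keeping a categorical time-by-treatment term would only reparameterise the same unconstrained model.

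The alternative is to model T2 and T3 as outcomes with the T1 score, by time and role, as a covariate and no longer as an outcome. Couples missing both follow-ups then contribute only through the planned multiple imputation; in the constrained model they stay in directly.

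The cost is a line of model specification, settled before any unmasked analysis. No new data, visits or participants are needed. If the expected gain is reported, give it as (1−ρ)/2 for a single visit with complete data, with ρ declared as an assumption.

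### The analysis model does not fix the randomisation strata: cancer type is off the covariate list, and sexual orientation must pass an outcome-significance screen

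*Protocol article*

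**What the plan says.** The Randomization section of the protocol article describes 1:1 allocation in blocks of 4, "stratified by cancer type (breast versus gynecologic) and sexual orientation reported by the cancer survivor (heterosexual versus other").

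The Statistical plan section then sets the covariates:

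- Candidates: "Covariates to be assessed include age, time since diagnosis, cancer stage, metastatic status, number of children, relationship duration, income, race, ethnicity, and sexual orientation". That is ten items. Sexual orientation is one of them; cancer type is not.
- Screening: "preliminary analyses will be conducted in which each outcome is predicted by the full set of qualifying covariates".
- Selection: "Only those covariates that predict at least one outcome significantly will be included in the analyses". No significance threshold is given.
- Use: once chosen, "the same set of covariates will be included in all analyses". The paragraph on exploratory Aim 1b carries this set into the mediation models.

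On the model itself, the section says that "time, treatment, and role will be treated as categorical, and models will include all main effects and interactions among these variables". It also says: "Evidence of treatment efficacy will be assessed by the interaction between time and treatment". Baseline is one of the three levels of time. No interaction of a covariate with time is mentioned, and nowhere does the article say that the strata are always in the model.

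**The concern.** Stratified randomisation balances the arms on the strata. An analysis that leaves the strata out ignores that balance, so its standard error is somewhat too large whenever the strata predict the quantity being compared. Here one stratum is not a candidate at all and the other is optional.

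The rule that decides the second stratum is also weak. It picks covariates by their p-values against the trial's own outcomes, and one hit among many outcomes is enough. The adjustment set is therefore unknown until outcome data are seen, and chance can admit irrelevant variables while a design factor stays out. The Discussion expects most participants to be heterosexual. The sexual-orientation contrast will then be imprecise, and whether it passes the screen will depend heavily on luck.

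At stake are the match between design and analysis, a little precision in the primary test, and the stability of the mediation estimates.

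**Working it through.** **The plan's own figures.** The plan gives no number for covariate adjustment. The nearest figure is the effective sample size for the treatment-by-time test, with a partner correlation of .4. It reproduces: 200/1.4 = 142.9 and 160/1.4 = 114.3, against the stated 142 and 114. It makes no allowance for covariates, so nothing below depends on it.

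**1. How often the screen keeps a useless covariate.** Table 2 lists 2 primary and 10 secondary outcomes, so 12. The threshold is assumed to be .05.

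- Independent outcomes: 1 − .95^12 = .46.
- Outcomes correlated .3 (simulation, 12 outcomes): .40.
- Outcomes correlated .5 (same simulation): .32.

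If all ten candidates were pure noise, the expected number kept would be 10 × .46 = 4.6, 10 × .40 = 4.0 or 10 × .32 = 3.2. In practice some candidates will be genuinely prognostic, so these counts describe the rule and do not forecast the trial.

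**2. What a main-effect covariate does to the primary contrast.** The contrast at 3 months is

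(mean OC at T3 − mean OC at T1) − (mean SS at T3 − mean SS at T1).

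A term γx that is constant over time for a person adds the same amount at T1 and T3, so it drops out when data are complete. The plan uses multiple imputation for these models, so each imputed data set is complete.

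A simulation of the stated model confirms this. It used 100 couples, two roles, three times, correlated intercepts and residuals, assumed variance components treated as known, and 150 runs:

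| Data | Covariates | Standard error of T3 contrast | Largest change in estimate |
|---|---|---|---|
| Complete | none | 0.2280 | – |
| Complete | orientation, age, cancer type as main effects | 0.2280 | 3 × 10⁻¹⁶ |
| Complete | same, plus their interactions with time | 0.2314 | 0.10 |
| 20% missing at T3, no imputation | none | 0.2464 | – |
| 20% missing at T3, no imputation | orientation, age, cancer type as main effects | 0.2465 | 0.05 |

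Only covariate-by-time terms act on the contrast when data are complete. With unimputed missing data, main effects move it by at most 0.05/0.2464, about 0.2 standard errors.

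The simulated covariates had no effect on change, so the time interactions could bring no gain. They cost 0.2314/0.2280 = 1.015, about 1.5% of the standard error. The simulation did not balance the arms on the strata, as the trial's randomisation would.

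**3. What ignoring the strata could cost.** If the strata explain a share R² of the variance in change and the arms are balanced on them, the unadjusted standard error is too large by a factor 1/√(1 − R²). The nominal 5% test then runs at 2[1 − Φ(1.96/√(1 − R²))].

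| Assumed R² | Standard error overstated by | Actual level of 5% test |
|---|---|---|
| .01 | 0.5% | 4.9% |
| .02 | 1.0% | 4.8% |
| .05 | 2.6% | 4.4% |
| .10 | 5.4% | 3.9% |

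The documents give no R². As a guide to plausibility, a single factor split 50:50 reaches R² = .05 only if change differs between its levels by 2√(.05/.95) = .46 within-level SD. R² = .10 needs 2√(.10/.90) = .67.

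**4. Mediation models.** These use the 3-month outcome as the end point, without the differencing over time in step 2. Covariates do not cancel there. The path from mediator to outcome is not protected by randomisation either, so the choice of covariates can move the indirect effects.

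**The case against.** The strongest reply is that the cancellation in step 2 also limits the complaint. If main effects drop out of the primary contrast, then omitting cancer type, losing sexual orientation or keeping several noise variables leaves that contrast as it was. This stands, and it rules out any claim that the screen distorts the primary result.

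Second, the article never says in words that covariates enter as main effects. That is inferred from the fact that it names interactions only among time, treatment and role. The form of the covariates may be set out in a fuller analysis plan. This stands as a qualification.

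Third, the larger precision figures need strata that strongly predict change. Differences of .46 to .67 SD exceed the effects of d = .27 to .36 that the trial is sized to detect, although the article does not say on which scale its d is defined. A factor with few people in one level explains little variance. The lower end of the range is more credible, and the error is in the cautious direction.

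Fourth, the rule does limit discretion: it names the candidates, states the criterion and uses one common set, which prevents tailoring by outcome. That is a fair credit. It does not answer the point about the strata. Even if the candidate list is read as open-ended, cancer type would still have to pass the screen.

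**Conclusion.** The concern holds in a limited form. The plan stratifies on two factors and then states a covariate rule under which one is not a candidate and the other depends on outcome p-values. This is a stated rule that does not match the design, not a detail left for later.

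A reader might infer that the primary test is biased, has an inflated type I error, or carries a seriously overstated standard error. The documents support none of these. Time-constant main effects cancel from the time-by-treatment contrast, exactly with complete or imputed data and nearly so otherwise. Ignoring the strata makes the test conservative, not liberal. The size of that loss is hypothetical: 0.5 to 1% of the standard error at R² of 1 to 2%, and 2.6 to 5.4% at R² of 5 to 10%, with R² assumed.

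Three things remain. The primary test does not reflect the stratified design. The screening step does no useful work for that test. The chance-selected set does reach the exploratory 3-month mediation models. The retention probabilities of .46, and .40 to .32, rest on an assumed .05 threshold and 12 outcomes. The change should be made, but the trial's main conclusion does not hang on it.

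**What to change.** - Include cancer type and sexual orientation, as randomised, in every model. Give each its interaction with time, and with role where role is modelled, so that the terms act on the contrast that is tested.
- Keep baseline as a level of time. Do not also enter the baseline score as a covariate: it is already part of the response, and adding it would require a different primary model.
- Delete the significance screen. Name any other covariates in advance on prognostic grounds, or use them only in a sensitivity analysis.
- Use the same fixed set in the mediation models.

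The cost is a few degrees of freedom. Each binary stratum takes 1 + 2 = 3 coefficients without role, and 3 × 2 = 6 when crossed with role, so 6 or 12 for the two. If the non-heterosexual stratum is small, its own coefficient will be imprecise. If the strata turn out unrelated to change, the extra terms bring no gain and may cost slight precision.
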